### Economic analysis

The cost-effectiveness in this study will be determined via calculating length of stay in days for the pregnant person both antepartum and postpartum and the length of stay for the baby.

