10	Postpartum endometritis	By diagnosis made within 7 days of birth	This outcome will be assessed via medical record review. The data will be available in the clinical record and treatment will be available in the medication chart
11	Infant born with 5-min Apgar scores < 7	By data imputed 5 min post-delivery	This outcome will be assessed via medical record review. The neonatal APGAR scores are recorded in the delivery summary
12	Infant born with abnormal cord blood lactate levels greater than or equal to 4.0	By data imputed from birth	This outcome will be assessed via medical record review. The neonatal cord blood gas readings are recorded in the delivery summary
13	Infants born with abnormal cord blood pH ≤ 7.10	By data imputed after delivery	This outcome will be assessed via medical record review. The neonatal cord blood gas readings are recorded in the delivery summary
14	Time to vaginal delivery	By birth of neonate	This outcome will be assessed via medical record review. The duration from start of oxytocin to delivery of the neonate will be calculated and presented as a median
15	Time from rupture of membranes to vaginal birth	By birth of the neonate	This outcome will be assessed via medical record review. The duration from start of rupture of membranes to the delivery of the neonate will be calculated and presented as a median
16	Neonatal intensive care unit (NICU) admission	By discharge from hospital of neonate	This outcome will be assessed via medical record review. NICU admission results in both a history and physical record and a discharge summary
17	Cost-effectiveness	By discharge of both mother and baby from hospital	This outcome will be assessed via medical record review. The cost of length of stay (in days) for both mother and baby will be assessed

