### Implementation {16c}

The randomisation is computer generated and outsourced to the Liggins Institute Clinical Data Research Hub. The research midwives and investigators who enrol participants do not have access to the randomisation schedule. People can consent to the study at admission to the hospital for induction of labour. At Te Toka Tumai Auckland, IOL patients are initially seen in the Women’s Assessment Unit and cervical preparation undertaken in that location. When they are found to have a favourable cervical examination, they await transfer to delivery unit.

Once a participant arrives on delivery unit and is ready to commence induction with oxytocin, the midwife caring for the participant on delivery unit accesses the computerised randomisation site. The study intervention is then assigned electronically.

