## Discussion

Recruitment for the trial commenced in June of 2021. During the first 18 months of the study, there were significant pandemic-related issues which impaired the recruitment rate. These included ‘silos’ of staff being created and discouragement of mixing across teams, hospital-wide shutdowns of research for weeks–months on three occasions and, lastly, inability of staff to perform recruitment as research was deemed a non-critical academic activity. Recruitment is now possible in the hospital, and staff have returned to study-related roles.

Internal barriers have been encountered, mostly related to the attitudes and beliefs of the clinical staff. The standard practice in New Zealand has for decades been the performance of amniotomy as soon as feasible, followed by oxytocin commencement. In spite of inconclusive data regarding duration of induction in the setting of amniotomy and the optimal timing of amniotomy, there is a lack of equipoise amongst the staff and potential recruiters. This has decreased buy-in from some lead maternity carers (LMCs) and their patients. Due to staff beliefs about timing of amniotomy during induction and labour duration, we have chosen hospital days as the element included in the cost-effectiveness analysis. One of the main factors causing care delays on our unit is lack of beds and suboptimal staffing of shifts. For this reason, length of stay is highly relevant locally.

A second barrier has been a commonly-held belief amongst both midwives and obstetricians that infusing oxytocin without performing an amniotomy increases the risk of amniotic fluid embolism (AFE). It is unclear what the basis for this belief is, but prior to trial start, the practice of early amniotomy was widely adhered to with the thought that it would prevent AFE. Now that educational sessions and individual discussions regarding the lack of evidence of risk with oxytocin infusion with intact membranes have been undertaken and the trial is underway with no findings to indicate a potential harm of delayed amniotomy, there has been increased momentum with recruitment.

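### The cost-effectiveness outcome is a hospital-stay or bed-cost comparison with no effect measure, and read plainly it counts stay before randomisation, which costs precision

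*Protocol article*

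**What the plan says.** Three places in the protocol article define this outcome.

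- Economic analysis fixes the method: cost-effectiveness rests on "length of stay in days for the pregnant person both antepartum and postpartum and the length of stay for the baby".
- Outcome 17 in the secondary outcomes table, labelled cost-effectiveness, says "The cost of length of stay (in days) for both mother and baby will be assessed".
- The Discussion gives the reason. Because of staff beliefs about amniotomy timing and labour duration, "we have chosen hospital days as the element included in the cost-effectiveness analysis". It adds that "One of the main factors causing care delays on our unit is lack of beds", together with staffing, and concludes: "For this reason, length of stay is highly relevant locally".

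The order of events is set out under Implementation {16c}. At this hospital, "IOL patients are initially seen in the Women’s Assessment Unit and cervical preparation undertaken in that location". Then: "When they are found to have a favourable cervical examination, they await transfer to delivery unit". Randomisation comes later: "Once a participant arrives on delivery unit and is ready to commence induction with oxytocin", the midwife opens the randomisation site. Screen failures confirms that this timing was deliberate, so that care before oxytocin could not differ by arm.

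Statistical methods {20a} adjusts secondary outcomes for the stratification variable (parity) and treats them as exploratory.

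**The concern.** There are two separate problems.

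First, the label promises more than the method delivers. A cost-effectiveness analysis relates a difference in cost to a difference in effect. Here the method is stated and contains only stay, or the cost of stay. If Late ARM lengthened stay but reduced chorioamnionitis, this outcome would show the cost of the policy but not whether the infections avoided justify it.

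Second, the quantity compared appears to include time that ended before allocation was known. That part of the stay cannot carry a treatment effect. It can only add person-to-person variation, and adjustment for parity alone is not designed to remove it. The comparison of bed use, which the Discussion says matters locally, would then be less precise than the same data allow.

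**Working it through.** **The label.** The three defining places were set side by side:

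- Economic analysis: maternal and baby days; no effect.
- Outcome 17: cost of those days; no effect.
- Discussion: hospital days as the chosen element; no effect.

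An illustration shows why the denominator matters. The largest cited trial (Background and rationale {6a}) reports 21.3 − 19.0 = 2.3 h longer from induction to birth with late amniotomy. Suppose, purely as an assumption, that this carried over into stay: 2.3/24 = 0.096 day per person.

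- At the design difference of 9% against 3%: 0.096/0.06 = 1.6 bed-days per case averted.
- At that trial's own 11.5% against 8.5%: 0.096/0.03 = 3.2 bed-days per case averted.

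The same difference in stay gives a ratio twice as large. Stay alone cannot distinguish the two situations.

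**The clock.** The article gives no mean, standard deviation or power figure for stay, so there is no stated figure to reproduce on this point. The number per arm is 250, from the recruitment goal of 500 in Sample size {14}. The standard deviations below are assumptions.

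Let S be the SD of stay after randomisation, P the SD of stay before it, and r their correlation. Then:

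- SD of total stay = √(S² + P² + 2rSP)
- SE ratio = SD of total stay / S
- SE of the difference = SD × √(2/250) = SD × 0.0894
- Minimum detectable difference at 80% power, two-sided 5% = (1.960 + 0.842) × SE

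With r = 0:

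| S (days) | P (days) | Variance factor | SE ratio |
|---|---|---|---|
| 2.0 | 0.5 | 1.06 | 1.03 |
| 1.5 | 0.75 | 1.25 | 1.12 |
| 1.0 | 1.0 | 2.00 | 1.41 |

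In the middle row:

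- The SE goes from 1.5 × 0.0894 = 0.134 day (3.2 h) to 1.677 × 0.0894 = 0.150 day (3.6 h).
- The efficiency loss is 1 − 1/1.25 = 20%.
- The minimum detectable difference goes from 9.0 h to about 10.1 h.

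For a true difference of 0.25 day with S = 1.0, power falls from 80% to 71% (P = 0.5) or 51% (P = 1.0).

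The result depends on r. With r = 0.3 the SE ratio is 1.10 for the first row and 1.61 for the last. A negative correlation would shrink the penalty, which vanishes at r = −P/(2S).

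**The unit.** Rounding to whole days adds a variance of about 1/12 = 0.083 day². At S = 1.5 the SE rises by √(1 + 0.083/2.25) − 1, about 2%; at S = 1.0, by about 4%. This is small.

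**The case against.** The strongest reply is that this is a loose label on the last of 17 exploratory outcomes, and that the rest is inference. Several parts of that reply stand.

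- **Clock start.** No sentence says that the antepartum count begins at admission. The full protocol or an analysis plan, neither shown here, may define it. Inclusion of earlier stay is the plain reading of antepartum combined with the stated sequence, not an explicit rule.
- **Bias.** A reader might infer that counting earlier stay biases the comparison. It does not: that time is fixed before allocation and balanced in expectation. Only precision suffers.
- **Bed use.** A reader might infer that the outcome cannot answer any useful question. The local question in the Discussion is bed occupancy, and stay in days addresses it. Choosing one resource item is disclosed and explained.
- **Days against hours.** A reader might infer that days are too coarse because labour differences are hours. But stay could also change through infection, caesarean birth or NICU admission, and the rounding penalty is small. Outcome 14 already measures oxytocin start to delivery for vaginal births.
- **Limits of the fix.** With S = 1.5 days, starting at randomisation still leaves a 95% half-width of 1.96 × 3.2 = 6.3 h. A difference of 2 to 3 hours would remain undetectable.

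The reply does not rescue the label. The article states how cost-effectiveness will be determined, so the absence of an effect measure is part of the stated method and not a detail left to another document. Nor does it give a reason to keep time before randomisation in the comparison.

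**Conclusion.** The point holds in a limited form. As written, the outcome is a hospital-stay or bed-cost comparison and cannot support a cost-effectiveness conclusion; this follows from the text and needs no assumption. On the plain reading of antepartum, it also counts stay that allocation cannot affect. That costs precision without bias: an SE increase of about 3% to 41% under the assumed SDs (1 to 2 days after, 0.5 to 1 day before, uncorrelated). The direction is sound unless the two parts of the stay are sufficiently negatively correlated; the size cannot be fixed from the article. The primary conclusion is untouched, and because the outcome is secondary and exploratory, importance is low to moderate.

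**What to change.** 1. Define maternal stay as the time from randomisation (or oxytocin start) to discharge. Report stay before randomisation separately as a baseline descriptor, or keep total stay and enter the earlier stay as a covariate.
2. Report the baby's stay separately, from birth to discharge.
3. Either rename the outcome hospital stay or bed cost, or relate bed cost to the primary outcome, which is already collected, as incremental cost per chorioamnionitis case averted, with its uncertainty.
4. Recording in hours is optional and brings little gain.

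The cost is a change of definition before data lock and a small amount of extra chart extraction of times. The article says trial data come from charts but does not confirm that every clock time needed is recorded there, so this should be checked first.

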### Interim analyses {21b}

No interim analyses are planned. The data safety monitoring committee have access to limited outcome data and to severe adverse event data.

### Methods for additional analyses (e.g. subgroup analyses) {20b}

There are no additional analyses presently planned. We plan ongoing input from our Māori investigator and will re-discuss any additional analyses as we review the trial data. Any additional analyses will be added to the statistical analysis plan prior to data lock.

### Methods in analysis to handle protocol non-adherence and any statistical methods to handle missing data {20c}

Data for individual outcomes will not be imputed. Missing data percentages will be reported for each outcome.

### Plans to give access to the full protocol, participant-level data and statistical code {31c}

The full protocol is available on the Australian and New Zealand Clinical Trials Registry. Participants may opt-in to receiving a copy of study results when they consent to participate in this trial. The dataset will not be made publicly available.

## Oversight and monitoring

### Composition of the co-ordinating centre and trial steering committee {5d}

The trial steering committee is comprised of the investigators, who respond to any recommendations of the DSMC. In addition to these investigators, the trial group also relies on feedback from research midwives hired to perform study procedures.

### Composition of the data monitoring committee, its role and reporting structure (21a}

The DSMC is comprised of a neonatologist (chair) and an obstetrician. The DSMC receives reports each 25% of recruitment detailing recruitment, withdrawals, limited outcome data and severe adverse events. The DSMC makes recommendations to the trial steering committee regarding ongoing trial maintenance, any data requests and any additions to the factors reported. Statistical analyses for reporting to the DSMC are performed confidentially by a non-clinical co-investigator who is not involved in any aspect of trial recruitment, patient care, or data collection.

### Adverse event reporting and harms {22}

Adverse events (AEs) are collected for each participant. The primary outcome, chorioamnionitis, is considered an AE in labour, as are antepartum haemorrhage, postpartum haemorrhage (> 500 mL), umbilical cord prolapse, maternal birth injury, neonatal birth injury and neonatal infections requiring additional care (NICU admission or antibiotic treatment). The occurrence of instrumental vaginal birth and caesarean birth are also collected. These outcomes do not require contemporaneous reporting to the DSMC. These outcomes will be reported in the trial results. Unexpected events identified by the investigators or research staff are recorded with the adverse event data and reviewed by the PI for inclusion as adverse events.

Severe adverse events (SAEs) are reported to the PI and also to the DSMC. Each participant’s medical record is checked for the SAEs. Severe adverse events are specified as follows: maternal admission to intensive care unit or equivalent, maternal death, stillbirth, early neonatal death (defined as within 28 days), neonatal encephalopathy. The SAEs will be reported in the trial results.

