### Concealment mechanism {16b}

While there is allocation concealment until the point of the trial intervention being performed, blinding of participants and clinicians and data extractors is not feasible for this study. Data analysis will be blinded to study allocation.

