## Assignment of interventions: blinding

### Who will be blinded {17a}

It is not feasible to blind clinicians or participants to the study intervention. The statistician will be blinded to the study intervention during the analysis.

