### Procedure for unblinding if needed {17b}

N/A. This study is not blinded.

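### Unlisted, non-severe events are classed as adverse events by a review with no stated criterion, by a principal investigator who probably knows the allocation

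*Protocol article*

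**What the plan says.** The section Adverse event reporting and harms {22} of the protocol article gives three routes by which a harm is captured.

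1. **Listed adverse events**, such as haemorrhage, cord prolapse, birth injury and neonatal infection, are collected for every participant along with mode of birth. The commitment is "These outcomes will be reported in the trial results".
2. **Listed severe adverse events** are also found by definition: "Each participant’s medical record is checked for the SAEs". They go to the PI and the data safety monitoring committee (DSMC) and are reported.
3. **Unexpected events** are those that investigators or research staff happen to notice. They are "recorded with the adverse event data and reviewed by the PI for inclusion as adverse events".

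On who knows the allocation, Concealment mechanism {16b} states that "blinding of participants and clinicians and data extractors is not feasible for this study". Who will be blinded {17a} adds "The statistician will be blinded to the study intervention during the analysis". The section on unblinding reads "N/A. This study is not blinded".

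**The concern.** In the first two routes, an event counts because it meets a description fixed in advance. In the third, whether it is classed as an adverse event turns on one person's judgement, made after randomisation and with no stated rule. Reviewing an event to assign its type or its relation to the intervention is routine. A review that settles whether the event appears in the harms table at all is a filter, and where the allocation is known that filter can work differently in the two arms.

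This matters here because early amniotomy is the hospital's standard care (Explanation for the choice of comparators {6b}). A period of oxytocin with intact membranes is therefore the newer practice, and its unforeseen harms are what the third route exists to catch. The Discussion describes a lack of equipoise among staff. It also reports a common belief that oxytocin with intact membranes raises the risk of amniotic fluid embolism. That event is on neither list, so it would be captured by definition only if it led to something listed, such as intensive care admission or death.

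**Working it through.** No figure in the plan depends on this point, and the sample size is unaffected. The check is mainly a comparison of sections.

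**Does the PI know the arm?** The document does not say so of the PI by name. The inference rests on three statements: the trial is declared not blinded, blinding of clinicians and data extractors is called not feasible, and the statistician is the only role described as blinded. Two further points support it. The Discussion reports protocol violations in the Late ARM group, so the trial team sees conduct by arm. The allocation is also the timing of membrane rupture, which an account of a labour event would often reveal.

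**Is there a rule or an independent check?**
- Criterion, masking or second reviewer for unexpected events: none stated in {22}.
- DSMC: "The DSMC receives reports each 25% of recruitment detailing recruitment, withdrawals, limited outcome data and severe adverse events". Unlisted non-severe events are not named. The committee may ask for additions to what is reported, and the content of the limited outcome data is not defined.
- Steering committee: made up of the investigators ({5d}).
- Audit: none planned ({23}).

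**Which events are exposed?** Only those that are not on the adverse event list, not on the severe adverse event list, and not captured by chart review as an outcome under Outcomes {12} (for example endometritis, low Apgar score, abnormal cord blood values or NICU admission).

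**Illustration.** The document gives no rate for unlisted events and no share that the PI would include, so all rates and shares below are assumptions. With 500 recruited 1:1, each arm has 250. Let p be the true rate, equal in both arms, and a and b the shares included in the two arms.

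Reported ratio = (p × b) / (p × a) = b / a. Expected counts are 250 × p × a and 250 × p × b.

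| p | a, b | Expected counts | Reported ratio (true 1.0) |
|---|---|---|---|
| 5% | equal (both 100%) | 12.5 v 12.5 | 1.0 |
| 5% | 90%, 70% | 11.25 v 8.75 | 0.78 |
| 5% | 90%, 50% | 11.25 v 6.25 | 0.56 |
| 2% | 90%, 70% | 4.5 v 3.5 | 0.78 |
| 10% | 90%, 70% | 22.5 v 17.5 | 0.78 |

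The distortion depends on b / a and not on the event rate. It can also hide a difference: with 10 v 5 true events and shares of 60% and 90%, the reported counts are 10 × 0.6 = 6 and 5 × 0.9 = 4.5. The ratio is then 6 / 4.5 = 1.33 in place of 2.0.

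**The case against.** **Excluded events are not shown to be lost.** A reader might infer that an event the PI rejects disappears before the blinded statistician sees the data. The document does not support this. It says unexpected events are recorded with the adverse event data and then reviewed, and nowhere says that a rejected event is deleted, withheld or left unreported. What stands is narrower: the text does not commit to reporting such events, and its natural reading is that the review decides which of them count.

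**No formal comparison is planned.** The regression analyses in {20a} cover primary and secondary outcomes, and {20b} plans no additional analyses. For harms the article promises reporting. This is correct, so the point concerns a by-arm tabulation and not a test or an estimated ratio.

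**The exposed set is residual.** This is also correct. A serious unforeseen event would usually surface as a listed severe adverse event or a secondary outcome.

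**This is a condensed article and investigator review is conventional.** The full protocol is said to be on the registry and may contain a criterion. Some review is needed to separate an adverse event from an ordinary feature of labour. Both points lower the weight of the concern. They do not remove it, because the article itself states a rule for these events, and that rule is a discretionary one.

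**Unblinded identification remains.** Staff who know the arm decide which events to notice and record. Changing the PI's step cannot correct that, and this part of the objection stands in full.

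**Conclusion.** The concern holds in a limited form. For unexpected events that are neither listed nor severe, classification as an adverse event depends on a review with no stated criterion, by someone who by inference knows the allocation. The tabulation of unlisted harms by arm could be affected. The primary outcome, listed adverse events and listed severe adverse events are not.

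The size and direction of any bias cannot be determined from the document. The ratios above show only what unequal inclusion would do, and equal inclusion does no harm. The conclusion rests on two assumptions: that the PI is not masked, and that the full protocol, not shown here, contains no rule for this review. It would be going too far to say that the harms results are biased or that events are being removed. This is a modest weakness in a stated rule, worth correcting because the correction is cheap.

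**What to change.** In Adverse event reporting and harms {22}, replace the clause "recorded with the adverse event data and reviewed by the PI for inclusion as adverse events" with wording to this effect:

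*All recorded unexpected events are tabulated by arm in the trial results. The PI's review assigns a category and states whether the event is judged an adverse event, with the allocation masked where feasible, and does not remove events from the tabulation.*

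The events are already recorded before review, so this needs no new data and can cover events noted since recruitment began. It can be adopted before data lock, the point up to which {20b} already allows additions to the analysis plan.

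The cost is a slightly longer harms table containing some minor events, plus some clerical work where descriptions can be masked. Masking will not always be possible, since a labour narrative often shows when the membranes were ruptured. The tabulation by arm is therefore the essential part. The trial report should also acknowledge that the events were identified by staff who knew the allocation, which this change does not correct.
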